### Expected risks

Whilst performing pulpotomy in vital primary molars diagnosed with irreversible pulpitis is a novel treatment, it is more conservative than the standard pulpectomy treatment. Pulpotomy can be considered as the first stage of pulpectomy and an effective emergency measure to manage pain associated with an infected pulp. Thus, we do not anticipate any significant safety concerns with the treatment interventions of this trial. The clinicians taking part in the trial are fully trained in the pulpotomy and pulpectomy techniques and all subjects enrolled in the trial will receive the usual standard of care treatment during and following the trial intervention. The trial site principal investigators (PIs) will record adverse events (AEs) and serious adverse events (SAEs) only if they have a reasonable casual relationship with the treatment interventions of the study. Rare but potential AEs and SAEs include perforation and hypochlorite injury. Patients who continue to experience pain following trial interventions will be able to access emergency care to address their symptoms. Trial site PIs will report AEs/SAEs to the trial co-ordinator who will escalate them as deemed necessary. AE reporting period for this trial begins upon enrollment and ends at the two-year follow-up period for participants.

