## Methods

### Trial design

This clinical study is a parallel, two-armed, open label, non-inferiority randomised controlled trial with a 1:1 allocation ratio between the experimental intervention arm (pulpotomy) and the active comparator arm (pulpectomy).

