### Follow-up timeline

Children enrolled in the study will be followed from the trial intervention until the end of the study (two years post-treatment). Trial participants and their parents/guardians will be initially contacted by phone 24 h after the treatment intervention to record their post-operative pain intensity score using the VAS. Post-operative pain intensity score will also be recorded 7 d after the treatment intervention before the placement of the SSC. Clinical and radiographic outcome data of the treated tooth will be recorded at 6 months, 12 months, and 24 months post-treatment. Children participating in the trial will be advised to continue their routine dental visits, with the recall period determined by their caries risk status. Any symptomatic visits to the dentist outside these follow-up timepoints will be identified and reason for the same recorded on the trial record form.

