### Blinding

Blinding of trial participants or clinical investigators will not be possible due to evident differences between the two trial interventions. However, post-operative clinical outcomes will be assessed by an experienced paediatric dentist who is blinded to the treatment allocation, while the radiographic outcomes will be independently assessed by two different paediatric dentists. An external researcher, not directly involved in the clinical part of the study, will generate the randomization sequence, provide the SNOSE for treatment group allocation, and perform the statistical analysis of the de-identified data.

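### Adverse events enter the record only after site investigators, who very probably know the arm, judge them treatment-related; procedural, non-dental and unrelated serious events can be lost

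*Protocol article*

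**What the plan says.** The rule is in the protocol article under Expected risks. Recording falls to the site principal investigators, and the condition reads: "serious adverse events (SAEs) only if they have a reasonable casual relationship with the treatment interventions of the study". The same sentence applies it to adverse events (AEs), so it covers AEs and serious adverse events (SAEs) alike. The word before relationship is evidently a misprint for causal. The same section sets the next step: "Trial site PIs will report AEs/SAEs to the trial co-ordinator who will escalate them as deemed necessary". It also states an expectation: "Thus, we do not anticipate any significant safety concerns with the treatment interventions of this trial". The AE period runs from enrolment to two years.

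On who knows the arm, Trial design describes a "parallel, two-armed, open label, non-inferiority randomised controlled trial with a 1:1 allocation ratio", and Blinding says "Blinding of trial participants or clinical investigators will not be possible due to evident differences between the two trial interventions". Under Allocation concealment, an independent allocator tells the clinical investigator the assignment. Under Randomisation and sequence generation, on-site investigators are kept unaware only of the block sizes and the sequence.

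Three other data streams carry no causality condition:
- Under Primary outcomes, a blinded dentist scores pain, tenderness, fistula, swelling and mobility. Follow-up timeline places this at 6, 12 and 24 months.
- Under Secondary outcomes, pain is scored at 24 hours and 7 days.
- Under Follow-up timeline, "Any symptomatic visits to the dentist outside these follow-up timepoints will be identified and reason for the same recorded on the trial record form".

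**The concern.** Safety data are normally logged first and attributed second, so that someone else can revisit the attribution. Here the order is reversed. An event that the investigator considers unrelated does not become an AE or SAE record, and no later analysis can restore it. Only events that pass this judgement reach the co-ordinator, and the article describes no independent or masked review of causality.

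The people who judge very probably know which treatment was given. The article calls pulpotomy for this indication novel, presents it as the more conservative option and expects little harm. Attribution made with that knowledge and expectation could differ between arms. What is at stake is the completeness of SAE capture in a trial in children, and the credibility of any AE counts shown by arm.

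**Working it through.** The plan gives no AE rate and no figure on this point, so there is nothing to reproduce. The check is a reading of the sections side by side, followed by an illustration under stated assumptions.

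**Step 1: is this a rule or an omission?** Expected risks makes relatedness a condition for recording. That is a stated rule, not a detail left to a fuller document, and no other section reverses it.

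**Step 2: does the person assessing causality know the arm?** Recording is assigned to site principal investigators. Blinding refers to clinical investigators. The article does not equate the two, but the open-label design, the disclosure of assignment to the clinical investigator and the narrow masking of on-site staff (blocks and sequence only) all point the same way. The blinded clinical assessor has no stated role in AE recording. This step is an inference, and a strong one.

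**Step 3: what escapes the other data streams?**

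| Event | Captured without a causality condition? |
|---|---|
| Clinical signs of the treated tooth at 6, 12, 24 months | Yes, by the blinded assessor |
| Pain at 24 hours and 7 days | Yes, as a score |
| Unscheduled symptomatic dental visit | Yes, with the reason |
| Procedural event that prompts no extra visit | No |
| Non-dental AE | No |
| SAE judged unrelated and handled outside dentistry | No |

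The last three rows are the gap.

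**Step 4: is there room for judgement that depends on the arm?** The article names hypochlorite injury as a possible event. Hypochlorite is applied to every tooth before allocation, and again as canal irrigation in the pulpectomy arm only. Whether a given reaction belongs to the trial interventions can therefore turn on the arm. For events before allocation is revealed, the arm is unknown when they occur. They still fall inside the AE period, so they need a place of their own in the listing.

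**Step 5: illustration.** Input from the document: 25 teeth per arm (50 split equally, Target sample size). Assumed: the true rate *p* of events that only the AE log would catch, equal in both arms, and the probability *r* that such an event is judged related.

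Expected recorded events per arm = 25 × *p* × *r*. The apparent ratio (pulpotomy to pulpectomy) is *r*₁/*r*₂, because 25 × *p* cancels.

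With *p* = 20%, 25 × 0.20 = 5 true events are expected per arm:

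| *r*₁ pulpotomy | *r*₂ pulpectomy | Recorded | Apparent ratio |
|---|---|---|---|
| 50% | 90% | 2.5 vs 4.5 | 0.56 |
| 60% | 80% | 3.0 vs 4.0 | 0.75 |
| 90% | 50% | 4.5 vs 2.5 | 1.8 |

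For *p* from 10% to 30% under these pairs, recorded counts run from 25 × 0.10 × 0.5 = 1.25 to 25 × 0.30 × 0.9 = 6.75 per arm. If *r* is equal in both arms the ratio stays at 1, but the share 1 − *r* of events is still lost: at 50%, 2.5 of 5 in each arm.

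**The case against.** The best defence is that the harms most relevant to these teeth are already collected, whatever their cause, and that the clinical signs are scored by someone blinded. This stands. A reader might infer that events judged unrelated vanish altogether; the outcome assessments and the visit log show that this is not so for dental symptoms. Nor does the visit log contradict the AE rule, since two logs may have different entry criteria. Its relevance is that recording without a causality condition is already practicable at this site.

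A second defence is that no comparison of harms is planned. This also stands. AEs are neither a primary nor a secondary outcome, and Statistical methods lists no test of them. A reader might infer that a planned safety analysis is biased; the article contains none. The filter would affect only such AE counts as are reported by arm.

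Third, the two complications that the article names are procedural, and their link to treatment will often be hard to dispute. This is partly right and limits the scope for differential attribution, but it does not help with unrelated SAEs or non-dental events.

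Fourth, the attribution probabilities above are assumed, and nothing in the document shows that attribution will differ by arm. That is correct. Losing equal numbers from each arm leaves the difference in counts unchanged. The confidence limit for zero events in a small arm would not fill this gap: it measures imprecision and would be the same if every event were logged.

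**Conclusion.** The point holds in a limited form and is worth correcting. The article makes relatedness a precondition for recording AEs and SAEs and gives the judgement to investigators who, by inference from the open-label design, know the arm. Procedural events that prompt no extra visit, non-dental AEs and SAEs judged unrelated would go unrecorded and could not be re-examined.

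The size of any distortion cannot be derived from the document. Under the assumed attribution rates, the apparent ratio ranges from 0.56 to 1.8 when the truth is 1, and the direction is unknown. The efficacy data do not pass through this filter, so the primary non-inferiority result and the pain outcome are unaffected. A reader might infer that the rule will favour pulpotomy because the article expects it to be safe; the documents do not support a direction.

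**What to change.** Replace the recording rule under Expected risks with text such as:

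> All AEs and SAEs from enrolment to the two-year visit will be recorded regardless of presumed cause. Relatedness will be recorded afterwards as a separate field, where feasible by the blinded clinical assessor already planned or from a description that masks the arm. All events and related events will be tabulated by arm, with events before allocation listed separately.

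Naming who judges relatedness matters. If the same unblinded investigators complete the new field, recording becomes complete but the tabulation of related events keeps the attribution problem. Masking will not always work, because an event during canal preparation reveals the arm; the tabulation of all events does not depend on that judgement.

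The cost is one amended statement, one extra form field and a few more entries in a 50-tooth trial. No treatment, visit or efficacy analysis changes.

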### Ethical considerations

Participants and their guardians will be invited to enrol in the trial voluntarily and will be assured that should they chose not to participate the standard treatment will be offered as normal with no prejudice. Study participants will be recruited to the trial only after obtaining the child’s verbal assent and their parents or guardians sign the Informed Consent Form containing detailed information about the study. Patients and their guardians will have the opportunity to ask questions and take any additional time they may need prior to their decision to participate. Participants and their guardians will be given the option of withdrawing from the study should they choose to do so at any time in the future.

### Dissemination

Study results will be reported according to the Consolidated Standards Of Reporting Trials (CONSORT) guidelines through conference presentations and scientific articles in peer-reviewed journals. Authorship of the publications emerging from this study will be determined based on the ICMJE guidelines. Any significant amendments to this study protocol will be reported when the study results are disseminated.

## Discussion

The proposed study is unique in that for the first time a non-inferiority RCT is evaluating whether the experimental pulpotomy treatment can prove to be no worse than the standard pulpectomy treatment for the management of symptomatic irreversible pulpitis in vital primary molars. Considering that pulpotomy has been shown to have highly successful treatment outcomes in vital mature permanent molars diagnosed with irreversible pulpitis, there exists the possibility of similar successful outcomes in primary molars too. Consequently, this trial has the potential to produce new knowledge and add information to an area that is currently under researched.

It is important to highlight that the root filling material proposed to be used in the pulpectomy intervention group (Endoflas) has among the highest success rates reported for primary root canal filling materials [31–35]. Similarly, the new generation MTA product proposed to be used in the pulpotomy intervention group not only retains the biocompatibility, immunomodulatory, osteogenic, and sealing properties of traditional MTA, but being a resin-free pre-mixed bioceramic has superior handling characteristics, faster washout and setting times [36, 37]. The NaOCl proposed to be used as the haemostatic/disinfection agent in the pulpotomy intervention group demonstrated comparable clinical/radiographic success to traditional pulpotomy medicaments like formocresol and ferric sulphate without their drawbacks [38–40]. The two-year follow-up period proposed in this study should be adequate to assess treatment success of the trial interventions in primary molar teeth. Studies with longer follow-up periods can be planned based on the initial results of this study.

If the hypothesis of the proposed study is confirmed, it will support the clinical application of more conservative treatment approaches to vital primary teeth with irreversible pulpitis. Such an approach has the potential to cause less pain and discomfort to paediatric patients, have a shorter chair-time, and lower the technical difficulty and cost of managing complicated pulp conditions in vital primary molars.

## Data Availability

Deidentified data sets that will be generated and/or analysed in the current study shall be made available from the corresponding author upon reasonable request. A summary of final findings, in layman’s language, will be made available to the trial participants.

## Abbreviations

AAPD: American Academy of Pediatric Dentistry
AE: Adverse Event
ASA: American Society of Anesthesiology
BSPD: British Society of Paediatric Dentistry
CONSORT: Consolidated Standards Of Reporting Trials
CTRI: Central Trial Registry India
GIC: Glass Ionomer Cement
ICMJE: International Committee of Medical Journal Editors
MTA: Mineral Trioxide Aggregate
RCT: Randomised Controlled Trials
SAE: Serious Adverse Event
SNOSE: Sequentially Numbered Opaque Sealed Envelopes
SPIRIT: Standard Protocol Items: Recommendations for Interventional Trials
VAS: Visual Analogue Scale
